#### PA consultations (12 weeks from baseline)

At the end of the 12 week intervention period the PA consultation will focus on encouraging participants to maintain any changes in walking behaviour. This will involve reviewing goals achieved and the perceived benefits of increasing walking behaviour, discussions about participants’ confidence levels (self-efficacy) about walking and a review of relapse prevention strategies that could help participants maintain increases in walking.

If a participant does not want to continue or increase their walking they will still be invited to participate in the data collection. However, if anyone expresses (verbally or non-verbally) a desire to withdraw from the study altogether, this will of course be respected. Written accessible resources on maintaining walking behaviours and PA levels will also be given to participants in the intervention group. These resources have been developed by the research team and include; a folder, a Walk Well information booklet, a step diary and a motivational DVD. There will also be a Walk Well information booklet provided for carers. Carers will be encouraged to revisit these materials regularly with participants.

### Outcome measures

#### Baseline measures

To identify any potential contraindications to the participant increasing PA, the Physical Activity Readiness Questionnaire (PARQ) [53] and demographic & health questionnaires will be completed at baseline only. If participants score positively on any item they will be advised to consult their GP about whether they should participate in the study. The following assessments will be completed by participants at the three data collection points.

#### Primary outcome - measures of PA

The primary outcome measure will be the change in average steps walked per day at 12 weeks from baseline. Secondary outcome measures will include; average number of minutes spent in PA per day (light, moderate and vigorous intensity), average time spent on sedentary behaviour per day.

To objectively measure walking behaviours and determine the time spent at various intensities of PA, all participants will be invited to wear accelerometers for seven days prior to the start of the intervention (visit two), at visit three (post intervention or control measurement) and visit four (follow up or post intervention). Actigraph GT3X accelerometers (Manufacturing Technology Inc., Florida) will be used. The accelerometer is worn at the hip, attached to a belt worn round the waist. Instructions will be given to wear the actigraph during all waking hours; except when showering, bathing or swimming. To monitor this, participants and carers will be asked to record the time when the actigraph was put on each day, any periods when it was removed, and the time it was removed prior going to bed. The actigraph has been shown to be a reliable and valid method to measure PA and sedentary behaviours [54]. Therefore, Actigraph GT3X accelerometers will measure steps taken per day, the amount of PA undertaken at light, moderate and vigorous intensity, and the amount of time spent on sedentary behaviour.

In keeping with guidelines on the validity of accelerometer data, the minimum data requirement will be set at six hours of data on at least three days from seven, to ensure a valid measure of PA levels [55]. The accelerometers will be set to record activity over 15 second intervals (epochs). Activity counts of four consecutive epochs will be summed to give activity counts for each minute. Published cut-offs will be used to express the accelerometer data as three categories of activity intensity; sedentary behaviour 0 – 499 counts per minute (cpm), light intensity activity 500 – 1951 cpm, moderate-vigorous intensity activity greater than 1952 cpm. In addition to the accelerometer data, the International PA Questionnaire-Short (IPAQ-S) will be completed by participants at all three data collection points. This will provide information about the types of activities that were undertaken. The Actigraph accelerometer and IPAQ-S have been used previously in a study involving adults with intellectual disabilities [56].

#### Secondary outcome measures

##### Well-being

Guidelines on the measurement on quality of life in adults with intellectual disabilities have been published and validated and measurement instruments developed [57].

To allow comparison with PA studies that do not include adults with intellectual disabilities as participants, the EQ–5D will be piloted as a measure of quality of life. The EQ-5D has been shown to be reliable, valid and sensitive to change in PA studies. The EQ–5D has been used as a proxy-measure of quality of life in studies involving adults with cognitive impairments due to stroke and dementia [58]. Due to the cognitive demands and the abstract nature of subjective ratings of quality of life, some adults with intellectual disabilities are unable to provide reliable subjective ratings. Since the target population of this study includes adults with the full range of intellectual disabilities, it might not be possible to collect subjective ratings of quality of life from all participants. Proxy rating and self rating of subjective quality of life have been reported to have poor agreement [59,60]. However, proxy report on objective measures on quality of life have adequate agreement with self ratings [59,60]. Hence, in this study, carers will be asked to complete the EQ–5D as a rating of the carer views of the five domains in the EQ-5D, rather than as proxy-rating. Individuals with mild intellectual disabilities will also be asked to complete the EQ-5D and the level of agreement with carer ratings examined.

To further capture any positive effects of physical activity on well being, overall vitality will be measured using the nine item Subjective Vitality Scale [61], modified for use by adults with intellectual disabilities.

##### Self efficacy

To measure changes is self-efficacy over the course of the intervention the Self-Efficacy for Activity for Persons with Intellectual Disability (SE-AID) [62] and Self-Efficacy for Exercise Scale [63] will be completed at all three time points.

##### Anthropometric measurements

Participants will be invited to have their weight, height and waist circumference measured. Measurements will be made with the participant wearing light clothes without shoes. All measurements will be made in duplicate and the final value calculated as the mean of the two measurements. Weight in kilograms (kg), will be measured to the nearest 100 grams (g), using SECA 877 scales (SE approval class III; SEA Germany). Height in metres (m) will be measured to the nearest 1 mm (mm) using the SECA Leicester stadiometer (SECA, Germany). The height (m) and weight (kg) will be used to calculate BMI using the formula; BMI = weight/height ^2^ (kg/m^2^). Waist circumference will be measured to the nearest 0.5 cm (cm) at the mid point between the iliac crest and the lowest rib, in full expiration when the participant is standing.

### Qualitative research

According to the MRC framework for the development and evaluation of complex interventions [46] qualitative research can be valuable for identifying what the important or “active ingredients” of an intervention are, and which elements are not related to the ‘treatment effect’. Therefore, semi-structured interviews will be carried out at the end of the trial. Participants with intellectual disabilities, who were able to understand and respond to questions regarding their PA participation, will be invited to take part in the qualitative interviews. Design of the set of tools has taken account of lessons learnt from previous work, taking in the views of people with intellectual disabilities, including guidelines approved by the Economic and Social Research Council (ESRC) [64].

Topics which will be covered include attitudes towards PA in general and walking in particular, including any changes in view over the 12-week intervention period, perceived benefits, drawbacks and impact of increased activity, subjective feelings of well-being before and after intervention and views about sustainability of exercise and benefit. If individuals are not able to participate in an interview, a carer or key worker will be interviewed instead. Data obtained from the latter will be treated as their views and not the proxy views of participants. With the respondent’s permission, the interviews will be recorded and transcribed. Otherwise, notes taken during interview will be written up in detail as soon as possible afterwards.

### Process measures

An in-depth process evaluation of the Walk Well intervention will be conducted following completion of the study. As recommended by the World Health Organisation [65], evaluation of health interventions is essential to inform the future implementation of effective and sustainable services. Process measures will be collected, guided by the RE-AIM framework for health interventions (Reach, Effectiveness, Adoption, Implementation and Maintenance) [66], in addition to recommendations by the World Health Organisation. Analysis of process data will provide insight into multiple aspects of the intervention, including; uptake, recruitment, promotion, effectiveness, delivery, training, resources, and sustainability.

### Data analysis

The primary outcome, change in average daily step count at the end of the intervention period (≈12 weeks) from baseline will be analysed using regression models taking account of clustering and adjusting for randomised group and baseline step count (i.e. random effects models).

Similar linear regression models will be fitted for each secondary outcome. Additional analyses may assess the effects of baseline characteristics on outcomes and investigate the evidence for interactions with treatment effects. All statistical analyses will be carried out according to a detailed Statistical Analysis Plan developed in collaboration with the Robertson Centre for Biostatistics, University of Glasgow, prior to unblinding of the randomised groups.

Analysis of interview data will involve a systematic approach set out by Holloway (1997) involving the following steps: ordering and organising the collected material, rereading the data, breaking the material into manageable sections, identifying and highlighting meaningful phrases, building, comparing and contrasting categories, looking for consistent patterns of meanings, searching for relationships and grouping categories together, recognising and describing patterns, themes and typologies, interpreting and searching for meaning. This process will be facilitated by using NVIVO, a widely used software package for ordering and coding (identifying themes) qualitative data.

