### Sample size

There is no data from walking intervention studies involving adults with intellectual disabilities on which to base a sample size calculation. The average step count/day of 6508 (SD ± 3296) of adults with intellectual disabilities in one study is similar to the baseline step count (6802: SD ± 3212) for participants in the “Walking for Wellbeing in the West” study (WWW) [40]. The effect size of the 12-week WWW in intervention was an approximate increase of 3,000 steps/day. To take account of the different population for this study, a target increase of 2,500 steps per day due to the intervention, and a standard deviation in the step count after the 12-week intervention of 3,500 have been used for the sample size calculation. For 80% power at the 0.05 significance level, 32 participants per group would be required. To allow for a drop-out rate of 20% over the course of the study, 40 participants in each group would be required.

However, individuals recruited may live together, attend the same day centres or community activities, and be supported by the same family or paid carers. These factors would make it difficult to randomise people living together, for example, to different arms of the study. Cluster randomisation will therefore be used, but this will affect the power of the study. There is no pilot data to inform the likely degree of clustering, but assuming a conservative intraclass correlation coefficient of 0.1, and an average of 3 participants per cluster, the study sample size would need to be increased by 20%. Therefore, taking a cautious approach, a total of 50 participants will be recruited into each arm of the study.

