#### Procedure

Following informed consent, a researcher will arrange a visit to collect baseline measures and provide participants with an accelerometer to wear for seven days. Individuals will be advised to continue with their normal PA while wearing the accelerometer. Accelerometer data will be used to assess baseline activity levels.

Participants will then be randomised into the active intervention or waiting list control group. For clusters of participants, the baseline data for all participants in the cluster will be collected before randomisation. The researcher will then telephone an interactive voice response system (IVRS; hosted by the Robertson Centre for Biostatistics, University of Glasgow) to register each group of participants in the study, by giving the participants’ screening number. After registering each participant, the system will notify the principal investigator of the allocation of the cluster (intervention or waiting list control). Randomisation will be stratified by the number of participants in the cluster (1, 2–3, > 4), to avoid an excessive imbalance between study groups.

Participants who are randomised to the intervention group will be contacted by the walking advisor and arrangements will be made for the first PA consultation. Individuals who are randomised to the waiting control group will be advised to continue with normal PA until they are contacted by the researcher for 12 week measurements. The researcher collecting the data will be blind to group allocation, therefore they will not know if the participant has received the intervention. Participants will again be given an accelerometer and asked to complete various questionnaires and anthropometric measures. Participants in the control group will then be offered the opportunity to take part in the intervention. Twelve weeks later (six months from baseline) all participants will be contacted and invited to meet the researcher to complete follow up measurements. Collection of data from participants 12 weeks after the end of the walking intervention will be used to examine whether any changes in PA are maintained. Participants will have the right to withdraw from the study at any time and to decline to take part in any particular aspect or measure. This will be explained to them while seeking consent and their on-going consent will be checked and assessed throughout the intervention. The procedure is illustrated in Figure 1 below.

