g) Randomisation into intervention group/ offer starting date (February 2013- Jan/Feb 2014)

Participants will be randomised into the walking intervention group or the waiting control group (randomisation by source of recruitment and level of intellectual disability).

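### The primary model as stated leaves out the stratification factor; its standard error is too large if 12-week steps still differ by stratum after baseline adjustment

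*Protocol article*

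**What the plan says.** **Model.** The outcome is defined under Primary outcome: "The primary outcome measure will be the change in average steps walked per day at 12 weeks from baseline". Data analysis states that it "will be analysed using regression models taking account of clustering and adjusting for randomised group and baseline step count", and identifies these as random effects models. The named terms are therefore randomised group, baseline steps and a cluster effect. Secondary outcomes get similar linear models. Other baseline characteristics appear only in optional additional analyses. All analyses are to follow a detailed SAP, which is not shown.

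**Randomisation.** Procedure says: "Randomisation will be stratified by the number of participants in the cluster (1, 2–3, > 4"). As printed, a cluster of exactly four falls in no stratum. Appendix 1, Stage 3, describes something else: "randomisation by source of recruitment and level of intellectual disability". Neither account is carried into the model.

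**The concern.** Stratified allocation forces the arms to be alike in the stratifying factor, so differences between strata largely cancel out of the treatment comparison. A model without that factor does not know this. It leaves the between-stratum variance in the cluster and residual components and reports a standard error larger than the true sampling variability of the estimate. Confidence intervals are then too wide, the type I error falls below 5%, and some power is given away.

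This happens only if the factor predicts the outcome beyond what the model already contains. Cluster size reflects shared homes, day centres and carers (Sample size section), and the Discussion and Challenges sections say that carer and social support shapes behaviour change. A residual stratum effect is therefore plausible, but no passage shows one. With 100 participants at three per cluster there are only about 100/3 ≈ 33 clusters, so precision is worth keeping.

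**Working it through.** **1. The plan's own figure.** Inputs from Sample size: "a target increase of 2,500 steps per day due to the intervention", "a standard deviation in the step count after the 12-week intervention of 3,500", 80% power, 0.05 (taken as two-sided).
- Normal approximation: n = 2 × (1.960 + 0.842)² × 3,500² / 2,500² = 30.8, so 31. The exact t calculation gives power 0.790 at 31 and 0.803 at 32. This matches "For 80% power at the 0.05 significance level, 32 participants per group would be required".
- Drop-out: 32 / 0.8 = 40, as stated.
- Clustering: 1 + (3 − 1) × 0.1 = 1.2, and 40 × 1.2 = 48, rounded up to 50.

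The sample size reproduces, and this point does not alter it.

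**2. Assumptions for the check (not in the documents).** There are 30 clusters and 94 participants: 8 clusters of size 1, 4 of size 2, 8 of size 3, 6 of size 5 and 4 of size 6. The SD is 3,500, the correlation between baseline and 12 weeks is 0.6, the ICC is 0.1, allocation is exactly balanced within strata, and there is no drop-out. The gap g is the difference in 12-week steps between adjacent strata at the same baseline. Because the model adjusts for baseline, the gap is the same for change as for 12-week steps.

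**3. Hand approximation.**
- Residual variance: 3,500² × (1 − 0.6²) = 7.84 million, split into 0.784 million between and 7.056 million within clusters.
- Size-weighted mean cluster size: Σm²/Σm = 390/94 = 4.15.
- With strata scored −1, 0, 1 (8, 32 and 54 participants), the variance of the score is 62/94 − (46/94)² = 0.42. An omitted stratum therefore adds 0.42g² to the between-cluster variance.
- SE² ≈ (4/94) × [7.056 + 4.15 × (0.784 + 0.42g²)] million, with g in thousands.
- g = 0: bracket 10.31, SE 662.
- g = 0.5: √(10.74/10.31) = 1.02. g = 1: √(12.05/10.31) = 1.08. g = 2: √(17.28/10.31) = 1.29.

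**4. Simulation of the stated model.** REML random intercept on change, adjusted for baseline, fitted with and without stratum; 1,500 runs per row, no treatment effect:

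| Residual gap per stratum step | SE, stratum omitted | SE, stratum included | Ratio | Type I error, omitted / included |
|---|---|---|---|---|
| 0 | 656 | 656 | 1.00 | 0.059 / 0.055 |
| 0, baseline gap 1,000 | 661 | 660 | 1.00 | 0.056 / 0.057 |
| 0, baseline gap 2,000 | 658 | 659 | 1.00 | 0.053 / 0.054 |
| 500 | 667 | 656 | 1.02 | 0.055 / 0.055 |
| 1,000 | 704 | 660 | 1.07 | 0.035 / 0.043 |
| 1,500 | 756 | 655 | 1.15 | 0.030 / 0.051 |
| 2,000 | 832 | 655 | 1.27 | 0.020 / 0.051 |

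At a gap of 1,000 the actual SD of the estimate is 666 without the stratum and 663 with it. The estimate is about equally precise either way; what is wrong is the reported standard error (704). A repeat simulation gave about 2%, 8% and 30% for gaps of 500, 1,000 and 2,000. The Monte Carlo error of a 5% rejection rate is √(0.05 × 0.95 / 1,500) ≈ 0.006, so 0.035 against 0.043 is not a clear difference; 0.020 against 0.051 is.

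Power for 2,500 steps, omitted against included: 0.949 and 0.948 (no gap), 0.934 and 0.951 (gap 1,000), 0.859 and 0.942 (gap 2,000).

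**5. What counts as captured by baseline.** In the baseline-gap rows, 12-week steps differ only as baseline predicts. A gap of 1,000 that persisted in full would leave 1,000 × (1 − 0.6) = 400 after adjustment. That is √(1 + 4.15 × 0.42 × 0.4² / 10.31) = 1.01, or about 1%.

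**The case against.** - **The SAP may already include the factor.** Complete covariate lists are commonly left to it, and the article does not say that its list is exhaustive. This stands as a limit on confidence. But the article does name the covariates of the primary model, and as named they do not match the design.
- **Nothing shows that cluster size is prognostic.** Procedure gives the aim of stratifying as avoiding excessive imbalance between groups, which may mean no more than balancing numbers. This stands: the loss is conditional and its size unknown. The variance consequence, if there is one, does not depend on the motive for stratifying.
- **The error is on the safe side.** This stands. In every scenario above, power stays over 80%.

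Three stronger readings are tempting, and the documents do not support them. A reader might infer that the standard error is inflated wherever step counts differ by cluster size. It is not, because the model adjusts for baseline steps and only the remaining difference matters. A reader might infer a biased or invalid primary result, or an underpowered trial; neither follows. And a reader might take cluster size as the settled factor, which Appendix 1 contradicts.

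**Conclusion.** The point holds in conditional form. The stated primary model omits the factor by which Procedure stratifies randomisation. The standard error is too large, and the test conservative, only to the extent that 12-week steps differ by stratum at a given baseline. The excess is about 2% for an assumed residual gap of 500 steps per stratum step, 7–8% for 1,000 and 27–30% for 2,000, and nil if there is no residual gap. These figures rest on the assumed cluster sizes, correlation of 0.6, ICC of 0.1, exact balance and no drop-out. The power values rest on the same assumptions and are not a forecast for this trial. It is a free improvement rather than an error that threatens the result, held with moderate confidence.

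**What to change.** 1. Reconcile Procedure (cluster size) with Appendix 1 (recruitment source and level of intellectual disability), and state which factors the randomisation system actually uses.
2. If cluster size is one of them, state the stratum to which clusters of exactly four belong.
3. Add the factors actually used as fixed effects in the primary random-effects model and in the similar secondary models, in both the analysis section and the SAP, before unblinding.

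The cost is a sentence of text and a few degrees of freedom: two for three cluster-size strata. If recruitment source is used, its three main categories in Appendix 1 also take two; the number of categories for level of disability is not given. No change to the sample size is needed. With no stratum effect the simulated standard error is the same with and without the factor (656 in both).

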## Discussion

The recent series of publications by the *Lancet* medical journal has drawn attention to the high prevalence or ‘pandemic’ of physical inactivity [67]. The series of papers highlight the harmful effects that physical inactivity and sedentary behaviour can have on the populations’ health and the environment. The need for research which focuses on increasing PA levels in specific population groups has been highlighted as an important step towards addressing this problem [68].

This paper presents the rationale and design of a RCT of a walking intervention for adults with intellectual disabilities. Since the RCT design is viewed as the optimal study design to minimise bias and provide the most accurate estimate of a complex intervention’s benefits [46], the design of this study is a key strength. As mentioned, the only other published walking intervention which has been carried out with adults with intellectual disabilities used an uncontrolled design and was carried out in an institutional setting [37]. Therefore, the Walk Well study will make an important contribution to the limited amount of work in this field. Since little is known about the feasibility of recruiting participants for walking programmes from organisations and services for people with intellectual disabilities, this study will help to identify the barriers and facilitators of using such an approach. This will be useful for future research in other PA or behaviour change programmes in this population.

Although interventions informed by the TTM have been shown to successfully support increases in PA and walking, relatively few studies have made use of the TTM to inform behaviour change interventions with adults with intellectual disabilities, many of whom have increased support needs around adaptive behaviour and experience significant social disadvantages. Furthermore, the complex health and social needs of adults with intellectual disabilities, the low baseline levels of PA and fitness [69] and the increased barriers to PA [70,71] suggests that some generic walking interventions may be inaccessible to adults with intellectual disabilities. Therefore, the design of this walking intervention for adults with intellectual disabilities is distinct from models used in previous general population studies. Consequently, exploring if components from the TTM model of behaviour change and SCT are relevant and applicable to PA in the lives of adults with intellectual disabilities is an important aspect of this study. Since these models of behaviour change recognise the importance of social support to change behaviour, they fit with the evidence-base on the importance to individuals with intellectual disabilities of support from friends, family, and paid carers, for healthy lifestyle choices and behaviours. Therefore, behaviour change theories and techniques provide a potential framework which is relevant to adults with intellectual disabilities’ lives and examining the role of family and paid carers in the process of behaviour change.

